##### Digestive complications

Mesenteric ischemia/ischemic colitis documented by CT and/or colonoscopic and/or surgical imagingDigestive tract hemorrhage (upper or lower), defined as the occurrence of hematemesis, melena, or rectorrhagiaPostoperative ileus, defined as a transitory (> 48 h) halt or slowing of intestinal transit

##### Hemorrhagic complications

Postoperative bleedingDisseminated intravascular coagulationTransfusion with blood derivatives: red blood cells, platelets, and fresh plasmaInflammatory systemic response syndrome, defined as the presence of at least two of the following criteria: (i) body temperature < 36 °C or > 38 °C, (ii) heart rate > 90 beats/min, (iii) respiratory rate > 20 cycles/min or a PaCO_2_ < 32 mmHg in a blood gas analysis, and (iv) leukocyte count < 4000/mm^3^ or > 12,000/mm^3^

##### Infectious complications

Surgical site infection, defined as the occurrence of wall infection (abscess or purulent discharge) or a documented bacterial infectionSymptomatic or asymptomatic postoperative urinary tract infection, defined as the presence of a germ (> 10^5^ CFU/mm^3^) in the urinePneumopathy, defined as new lung infiltrates plus at least two of the following: (i) fever > 38.5 °C or hypothermia < 35.5 °C and (ii) leukopenia < 4000 WBCs/mm^3^ or hyperleukocytosis > 12,000 WBCs/mm^3^Purulent secretions. Bacteriological confirmation will be made by the presence of microorganisms in bronchial samples (sputum culture > 10^7^ CFU/mm^3^, bronchial aspirate > 10^5^ CFU/mm^3^, bronchoalveolar lavage > 10^4^ CFU/mm^3^, distal protected aspirate or protected specimen brush > 10^3^ CFU/mm^3^)Bacteremia, defined as the presence of a positive blood culture for a pathogenic germInfection of a catheter (central venous or arterial), defined as a positive culture of the same microorganism on the catheter (> 10^3^ CFU ml^−1^) and in at least one peripheral blood sampleSepsis, defined as life-threatening organ dysfunction caused by a dysregulated host response to infection. For clinical application, organ dysfunction can be represented as an increase in the Sequential [Sepsis-related] Organ Failure Assessment (SOFA) score of 2 points or more, which is associated with an in-hospital mortality rate above 10%Septic shock, defined as a subset of sepsis in which particularly profound circulatory, cellular, and metabolic abnormalities are associated with a greater risk of mortality than for sepsis alone. Patients with septic shock can be clinically identified by the requirement for vasopressor to maintain a mean arterial pressure (MAP) of > 65 mmHg and a serum lactate level greater than 2 mmol/l (> 18 mg/dl) in the absence of hypovolemia [23]

*Death* during hospitalization, on POD30, and at 1 year. Each patient’s vital status will be documented via a telephone call 30 days after surgery.

The secondary outcomes are:
The mean length of stay in each group: the postoperative length of stay in the intensive care unit (ICU) (days) and the overall length of hospital stay (the number of days spent in the hospital until discharge)The proportion of patients with complications within the 7 days following surgery in each groupThe mortality rate on POD30 in each groupThe mean total intraoperative IV fluids administered (crystalloids and colloids) in each groupThe mean laboratory criteria (plasma creatinine, lactate, C-reactive protein (CRP), troponin Tc, and brain natriuretic peptide (BNP) and the SOFA score in each group, measured on POD1, POD2, and POD7)

### Participant timeline {13}

The inclusion period is expected to last for 48 months. Several visits are provided for in the protocol. The visits take place when the patient is hospitalized, on the day of inclusion/surgery (POD0), POD1, POD2, POD7, and POD30 (Fig. 1). The visits on POD0, POD1, POD2, and POD7 must be performed on the scheduled day. For the visit on POD30, a margin of 5 days before D30 and 5 days after D30 will be tolerated.

#### Allocation

The patients will be randomized by an investigator named in the protocol. After checking the patient’s inclusion criteria and consent, the investigator connects to the secure (SSL) website https://recherche-clinique.chu-amiens.fr/CSOnline/ and creates a patient file in the database (assignment of the patient code). The investigator will have to enter the requested data in order to check the inclusion and noninclusion criteria. If all the requested data are entered and are consistent, the investigator will be given the result of the randomization as either “standard management” or “RER.” If any of the data are erroneous or data, an error message will indicate which corrections must be made so that the patient can be randomized.

#### Follow-up visits

Five follow-up visits are planned: on the day of inclusion/surgery (POD0), POD1, POD2, POD7, and POD30. The visits on POD1, POD2, POD7, and POD30 will be performed by an anesthesiologist who is blinded to the group allocation and has not managed the patient in the operating theater. These visits enable the progressive, consecutive collection of the study data.

Participation in the study will not change how patients are managed during their stay in the ICU and in hospital generally, other than compliance with the hemodynamic optimization protocol. As part of their care, patients always provide several blood samples—including at least one per day during the first week.

#### End-of-study visit

The end-of-study visit takes place on POD30. The purpose of this visit is to collect study data generated since the previous visit (POD7). The variables documented will be the same as those documented at the POD7 visit. The end of the study is defined as the last study visit by the last person participating in the study. No particular post-study treatments are planned for study participants.

### Study timeline for participants

### Sample size {14}

According to the literature data, the postoperative complication rate in the target population is between 30 and 50% [24]. The inclusion of 170 patients in each arm would show that RER-based hemodynamic optimization reduces these complications in a clinically significant manner (by a third; from 50% in the control group to 35% in the interventional arm). These calculations were performed with an alpha risk of 5%, a power of 80%, and a complication rate of 50% in the control arm.

Furthermore, an interim analysis is planned halfway through the inclusion process. Hence, the final study population should be 344 patients. Based on these results and after taking account of potential loss to follow-up, we plan to include 350 patients (175 per arm). If 175 patients are included in each arm, the threshold for statistical significance in a one-sided test will be set to *p* < 0.003 (according to the Lan and Demets spending function, using the seqdesign SAS procedure). Premature study termination for efficacy could thus be considered.

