##### Analysis of the primary outcome

The null hypothesis will be rejected in favor of the alternative hypothesis (i.e., there is a difference) using a chi-squared test or Fisher’s test, depending on the frequency of complications (*n* < 5 in a cell of the contingency table), with a two-sided alpha risk of 5%.

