##### Analysis of the secondary outcome

The two arms will be compared with regard to the total volume of intraoperative fluids and the length of stay, using Student’s test or the Mann-Whitney test for normally distributed data.

The two arms will be compared with regard to the changes over time in the SOFA score and the serum NT-pro-BNP, troponin TC, CRP, lactate, and creatinine levels, using a mixed-model analysis of variance. Post hoc comparisons will be performed after Hochberg adjustment. If the data are not normally distributed, they will be log-transformed or otherwise transformed.

The intergroup difference in the incidence of each complication (including mortality) will be compared in a chi-squared test or Fisher’s test.

All statistical analyses will be performed using SAS® software (version 9.4). The threshold for statistical significance will be set to *p* < 0.05 for both the primary and secondary outcomes. The statistical criteria for premature termination of the study are listed above in the statistical analysis section (*p* < 0.003).

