#### Interim analyses {21b}

An interim analysis is planned half way through the inclusion process (*n* = 175 out of 350).

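### The final primary test keeps the full 5% after an efficacy look, and the interim threshold of 0.003 is given a side and a sample size that conflict with other sections

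*Protocol article*

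**What the plan says.** All references are to the protocol article.

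- **Sample size {14}.** The design is sized to detect a fall "from 50% in the control group to 35% in the interventional arm". On the error rates and the control rate, the section adds: "These calculations were performed with an alpha risk of 5%, a power of 80%, and a complication rate of 50% in the control arm". This gives "The inclusion of 170 patients in each arm". An interim look halfway through inclusion is then allowed for: "Hence, the final study population should be 344 patients", rounded up to 350 for loss to follow-up. The section continues: "If 175 patients are included in each arm, the threshold for statistical significance in a one-sided test will be set to" p < 0.003, attributed to the Lan-DeMets spending function in the SAS seqdesign procedure, and says that the trial could stop early for efficacy.
- **Analysis of the primary outcome.** A chi-squared or Fisher test is used, "with a two-sided alpha risk of 5"%.
- **Analysis of the secondary outcome.** The closing paragraph sets the significance threshold at p < "0.05 for both the primary and secondary outcomes". It repeats p < 0.003 as the criterion for early termination, without a side.
- **Interim analyses {21b}.** "An interim analysis is planned half way through the inclusion process", at 175 patients out of 350.

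No reduced threshold for the final primary test is printed anywhere in the article.

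**The concern.** A spending function divides the overall 5% between the looks. Whatever the interim look spends is no longer available at the end, so a final test at the full 0.05 cannot belong to the same plan as an efficacy boundary drawn from that function. Here one section invokes the function and another fixes the final primary threshold at 0.05.

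Two labels on the interim threshold add to the difficulty. It is called one-sided although the primary test is two-sided, and it is attached to 175 patients in each arm, which is the whole trial, although the look takes place at 175 patients in total (about 87 per arm).

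At stake is error control for the confirmatory test. A final p-value just under 0.05 could be declared significant when the spending plan would not allow it. At the interim, those who monitor the trial would not know whether the bar is 0.003 or 0.006 on the two-sided scale. The Trial status section reports 120 patients randomized, so at that date the look had not been reached.

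**Working it through.** **Inputs.** Rates of 50% and 35%, power 80%, alpha 5%, 170 per arm, 344 and 350 in total (Sample size {14}); two-sided test (Analysis of the primary outcome); look at 175 of 350, so information fraction t = 0.5 (Interim analyses {21b}); final p < 0.05 (Analysis of the secondary outcome). *Assumption:* the Lan-DeMets function is of O'Brien-Fleming type, because the article names only the family.

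**1. The plan's own sample size.** With pooled rate 0.425 and a two-sided 5% test:

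n = [1.960·√(2·0.425·0.575) + 0.842·√(0.50·0.50 + 0.35·0.65)]² / 0.15² = 169.3, so 170 per arm.

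This matches. A one-sided 5% test would need 134 per arm, so the design was sized two-sided.

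**2. The interim boundary.** Spending 0.025 per side at t = 0.5:

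α(0.5) = 2·[1 − Φ(2.2414/√0.5)] = 0.00153 per side, so z₁ = 2.963.

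The two-sided value is 2 × 0.00153 = 0.00305. The printed 0.003 therefore agrees with the two-sided value; the one-sided equivalent is 0.0015. A one-sided 5% design would give 0.0056, which does not agree.

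**3. The final boundary that goes with it.** The statistics at the two looks are bivariate normal with correlation √0.5. Solving P(Z₁ > 2.963 or Z₂ > z₂) = 0.025 gives z₂ = 1.969, that is two-sided p < 0.0490. The required inflation of the sample size is 1.0037, and 340 × 1.0037 = 341.3. The stated 344 is close to this and slightly above it.

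**4. Overall type I error with the final test left at 0.05.** For symmetric boundaries this is 1 − P(|Z₁| < c₁, |Z₂| < 1.960).

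| Reading of 0.003 at the interim | c₁ | Overall type I error |
|---|---|---|
| Two-sided 0.003 | 2.968 | 5.10% |
| One-sided, stop for benefit only, final test two-sided 0.05 | 2.748 | 5.12% (benefit side 2.62% against 2.50%) |
| 0.003 on each side | 2.748 | 5.24% |
| Both looks one-sided (0.003, then 0.05) | 2.748 | 5.07% |

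The last row contradicts the two-sided primary test and is included for completeness. Every row exceeds 5%.

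**5. Final threshold by side.** If the interim 0.003 is two-sided, the final two-sided threshold that restores 5% is 0.0490. If 0.003 applies per side (0.006 two-sided), it is 0.0476 (z = 1.981).

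**6. What the side changes at the interim.** At 87.5 per arm with true rates of 50% and 35%, the z = 2.963 boundary needs an observed difference of about 22.1 points and is crossed with probability 16.7%. One-sided 0.003 (z = 2.748) needs about 20.5 points and is crossed with probability 22.7%.

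**The case against.** The strongest reply is that little of this is demonstrably an error.

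*The interim value.* A reader might infer that the boundary is wrong and spends twice the permitted alpha on the benefit side. The document does not support that. The conclusion needs an O'Brien-Fleming-type function at 0.025 per side, and only the Lan-DeMets family is named. Other conventions come out near a one-sided 0.003: the same formula spending 0.05 in total over both sides gives 0.0056/2 = 0.0028 per side, and the classical O'Brien-Fleming boundary (z = 2.797) gives 0.0026 per side. Both round to 0.003, so the one-sided label may be deliberate. What stands is that the label must be reconciled with the two-sided 5% test. Under these two conventions the final threshold is about 0.048, which is still not 0.05.

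*The sample size attached to it.* A reader might also infer that 0.003 governs the full-sample analysis, with a serious loss of power. That does not hold either. The same section introduces the look as halfway and links the threshold to early stopping, and the secondary-outcome section assigns 0.003 to early termination and 0.05 to the final test. The 175 per arm is probably the design size from which the boundary was derived. It remains badly worded.

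*Size.* The excess is comparable with the discreteness of the test itself. For a single final look at 175 per arm, the exact size of the chi-squared test at nominal 0.05 is 5.06% at a common event rate of 30%, and 4.78% at 42.5% and at 50%. At 50%, moving to 0.049 leaves it at 4.78%. This is a fair reason not to rate the point as critical. It does not reconcile a spending function with an unreduced final threshold.

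*A fuller document.* The full protocol or an analysis plan may give the function type and the final bound, and leaving those out of an article would be no fault. But the article is not silent on the final threshold: it prints 0.05 for the primary outcome.

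**Conclusion.** The point holds in a limited form. The article spends alpha on a halfway efficacy look and still judges the final primary test at the full 0.05, so the overall type I error is above the stated 5% under every reading of 0.003: 5.10% to 5.24% with a two-sided final test, and 5.07% if both looks were one-sided. The excess of roughly 0.1 to 0.2 percentage points comes from the unreduced final threshold. In practice it affects only a final p-value between about 0.048 and 0.05.

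The one-sided label and the reference to 175 per arm are conflicts of wording with the primary-analysis and interim-analysis sections. Of the two, the side matters more, because it shifts the stopping criterion by about 1.6 points of observed difference (22.1 − 20.5). The number 0.003 itself is not shown to be wrong, and the sample size reproduces.

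The error rates rest on the normal approximation and a look at exactly half the information. The match of 0.003 to a two-sided boundary also rests on O'Brien-Fleming-type spending. The point is worth correcting, but it does not threaten the trial's conclusions unless the result is borderline.

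**What to change.** - **Sample size {14} and Interim analyses {21b}:** name the type of spending function. State that the look takes place at 175 patients in total (about 87 per arm) once their day-7 outcome is complete, and remove the link to 175 per arm.
- **Side of the interim threshold:** give 0.003 a side consistent with the two-sided primary test. Under the usual O'Brien-Fleming-type function this is two-sided p < 0.003.
- **Analysis of the primary outcome and Analysis of the secondary outcome:** for the primary outcome, replace 0.05 as the final threshold with the value that matches. This is two-sided 0.049 if 0.003 is two-sided, or about 0.0476 if 0.003 is truly one-sided. The 5% can remain as the overall level.
- **Timing:** state that both bounds are recomputed from the same function if the look falls at a number other than 175.

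The cost is a change of wording and a slightly stricter final threshold. The sample size is unchanged: 344 already allows for the look, and 350 are planned.

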### Recruitment {15}

The feasibility of this project is guaranteed by (i) the relatively large number of potentially eligible patients treated in the various centers and (ii) the involvement of a multicenter group whose members have been working together on hemodynamic optimization research projects for many years.

Number of eligible patients per center:

Amiens University Medical Center: 2 to 3 inclusions per month

Lille University Medical Center: 1 inclusion per month

Caen University Medical Center: 1 inclusion per month

Dijon University Medical Center: 2 to 3 inclusions per month

Valenciennes General Hospital: 1 inclusion per month

### Assignment of interventions: allocation

#### Sequence generation {16a}

Patients will be randomized into the two parallel, open-label groups using Clinsight® software, as implemented by a data manager from the Clinical Research and Innovation Directorate at Amiens University Medical Center. Randomization by minimization will be performed.

The randomization will be stratified:
By centerBy the type of surgery (orthopedic, vascular, or abdominal)

Patients will be randomly assigned to one of the study groups via centralized randomization by minimization, in order to check for stratification factors and balance the size of the groups. This will also make it possible to check patient eligibility and send randomization information to the investigator for each patient.

After entering their username and password, the investigators will connect to the study randomization site on the day of inclusion and check compliance with the inclusion and noninclusion criteria. If no inconsistencies are found, the result of the randomization will be displayed as “standard management” or “RER.”

#### Concealment mechanism {16b}

Prior to the provision of informed consent, participants (and, if applicable, their legal guardians) will be given full information about the study by the researchers at each study site. The provision of study information will be recorded in the Clinsight® software by the research assistants. After the baseline survey, eligible participants will be randomized 1:1 into two groups.

#### Implementation {16c}

The pre-inclusion visit is carried out by an investigator named in the protocol. It will take place during the PAC. All selected patients meeting all the inclusion criteria and none of the noninclusion criteria will be invited to participate in the study.

### Assignment of interventions: blinding

#### Who will be blinded {17a}

Although the operating anesthetists cannot be blinded to group assignments, much attention will be given to ensuring strict blinding during the postoperative, data collection, and data analysis periods. The surgeons and ICU physicians and nurses are blinded to group allocation. Only the anesthetist in charge of the patient during the surgery will be aware of the group allocation.

#### Procedure for unblinding if needed {17b}

An unblinding procedure is not necessary and not planned.

### Data collection and management

#### Plans for assessment and collection of outcomes {18a}

All data will be continuously recorded on an electronic case report form (eCRF) by a clinical data manager who is blinded to the group allocation. The eCRF was created by study investigators. All the information required by the protocol must be recorded as and when it is obtained in the eCRF, and any missing data must be explained:
“NK” for “not known”“ND” for “not determined”“NA” for “not applicable”

Any access to the study data and any changes will be tracked by the Clinsight® software (Ennov Clinical).

Preoperative data
Demographic dataMedical history (high blood pressure, diabetes, kidney failure, etc.), and the indication for surgery (neoplastic disease or not)Preoperative laboratory assessment (including plasma creatinine and CRP levels)Drug treatments (antihypertensive drugs, antidiabetics, diuretics, etc.)Intraoperative data
*Anesthetic data:*IHypnotics, opioids, and muscle relaxants usedIIVolume of fluids (crystalloids and colloids) usedIIINumber of labile blood products used
(b)*Hemodynamic data (every 30 min):*ISAP, DAP, and MAPIIHeart rateIIIBispectral indexIVTemperatureVCardiac outputVIPulse pressure variationVIITotal amount of ephedrine and norepinephrine usedVIIITotal amount of dobutamine usedIXIntraoperative diuresis
(c)*Surgical data:*ISurgical indication and type of surgery (abdominal, vascular, or orthopedic)IIDuration of surgeryIIIVolume of blood lossIVIntraoperative surgical complications

3.Postoperative dataLength of stay in the recovery roomPatient discharge (to a surgical department, the ICU, or the recovery room)Laboratory assessment:IKidney function: serum creatinine and urea levels on POD1, POD2 and POD7, and renal replacement therapyIIBlood lactate and plasma creatinine, CRP, BNP, and troponin Tc on POD1, POD2, and POD7(d)Standard clinical data (heart rate, blood pressure, peripheral O_2_ saturation, and respiratory rate)(e)Diuresis on POD1, POD2, and POD7(f)KDIGO scores on POD1, POD2, and POD7(g)Postoperative complications(h)Length of stay in the ICU and in hospital(i)30-day postoperative mortality

#### Plans to promote participant retention and complete follow-up {18b}

At each visit, participants will be reminded of the importance of their participation in the study and the need to be continuously contactable and available for monitoring until the end of the follow-up period. We will make sure that appointments for study visits are available at different times of the day and on different days of the week. Saturday visits will also be available for participants who cannot attend during the week.

Participants who withdraw from the trial will be contacted (with their prior permission) by phone on POD30 in order to check on whether they have developed postoperative complications.

#### Data management {19}

All data will be continuously recorded on the eCRF by a clinical data manager who is blinded to patient allocation. Data collected directly during the patient’s follow-up will be entered (single-entry) into an electronic case report form by the principal investigator (or by authorized persons referenced on the task delegation list) on the https://recherche-clinique.chu-amiens.fr/CSOnline/ website.

The pre-configured consistency tests will check the quality of the data. If inconsistencies are detected, queries will be sent to the investigator.

The data coding will be given on a separate sheet in the electronic case report form. Data will be entered initially as the actual numerical value or the actual categorical variable.

At the end of the study, the Clinsight® database (Ennov Clinical) will be frozen by a data manager at Amiens University Medical Center’s Clinical Research and Innovation Directorate. The centralized data will then be analyzed using SAS® statistical software (version 9.4, SAS Institute Inc., Cary, NC, USA).

